### TTNS Intervention: 

**Type of equipment**: Stimulation of posterior tibial nerve will be delivered by Transcutaneous Electrical Nerve Stimulation (TENS) unit.
**Application of TTNS:** based on the anatomical distribution and previous reports: the anode will be positioned between 5–10 cm above medial malleolus and posterior to the edge of the tibia and the cathode will be positioned distally on arch of the foot (
Castel-Lacanal, 2015;
Mcguire *et al*., 1983). The accurate location of electrode is considered by contractions of the appropriate muscles innervated by posterior tibial nerve; sensory response by tingling sensation of sole of the foot and / or motor response by flextion of big toe and fanning of the other toes.
**Patient position**: participant will be advised to lie supine with extended legs or supported sitting with knee extension in order to allow the nerve roots to be free from any compression at knee joint.

Participants will be advised to ensure that their skin is clean skin under the electrode to minimize skin resistance. In cases where participants apply skin mosturiser, they will be advised to wipe the area with alcohol swap or with soap and water and ensure the area is completely dry prior to electrodes application.

**Duration of Treatment:** A six weeks intervention period has been shown to be effective among a neurogenic population (
Monteiro *et al*., 2014) and preferable among participants who has been interviewed during phase II study
*(
[name] et al., 2019)*

**Side of Lower leg**: based on physiology of the central nervous system control of the bladder we would use the left ankle for the application of TTNS because it has been shown that the right side of the brain is the predominant active area in micturition (
de Groat, 1997;
Sand & Sand, 2013).
**Frequency:** 10 HZ. It has been shown that low frequency of 10HZ is effective in inhibiting sympathetic nervous system that might normalize bladder functions (
Robertson *et al*., 2006).
**Intensity:** the intensity of stimulation will be at the sensory and motor threshold by tingling sensation on sole of the foot with flexion of big toe and /or fanning of other toes. The stimulation should not be painful (
Zecca *et al*., 2014).
**Pulse duration**: 200 microseconds, it is important to be long enough to allow action potentials to leave the hyperpolarization zone induced by anodic phase (
Vargas Luna *et al*., 2017). It is consistent with previous studies.
**Stimulus duration:** 30 minutes
**Frequency of treatment**: 3 times/ week for 6 weeks

### Outcomes

**Primary outcome measures**. A) Feasibility will be assessed by the proportion of participants who: are recruited to the study, complete assigned outcome measures, complete the 6-week intervention, and are lost to follow up. Also, feasibility will be assessed by the overall level of adherence achieved over the study period of 6-weeks through the self-report diary (
Anghel *et al*., 2019). Adverse events will be measured using a self-report diary and will include (but will not be limited to) any device related skin redness at the site of stimulation, discomfort at the stimulation site that might persist post treatment session. B) Acceptability (satisfaction) of TTNS application will be assessed using a self-report questionnaire developed by the researchers containing 5-point Likert scales: 1= “strongly disagree”; 2= “disagree”; 3= “neutral”; 4= “agree”; 5= “strongly agree”.

**Secondary outcome measures** include the followings:

The storage symptoms will be assessed by ICIQ-OAB (
Abrams *et al*., 2018;
Zappavigna & Carr, 2015). It has grade A for validity, reliability and responsiveness to change established with rigour on one data set. The total score ranges from 0 to 16 with higher values indicating increased symptom severity. Bother scales are not incorporated in the overall score (
Abrams *et al*., 2006).Severity of frequency, nocturia, and incontinence will be assessed by using a standard 3-day bladder diary (
Jimenez-Cidre *et al*., 2015;
Nambiar & Lucas, 2014). Number of episodes of frequency, nocturia, and incontinence/ 72 hours will be calculated and compared from baseline with higher values indicating increased symptom severity.Severity and intensity of urgency will be assessed using Patient Perception of Intensity of Urgency Scale (PPIUS) (
Notte *et al*., 2012). Number of urgency episodes and severity of urgency/72 hours will be calculated and compared from baseline. The total score ranges from 0 to 4 with higher values indicating increased symptom severity.Quality of Life (QoL) will be evaluated by using King’s Health Questionnaire (
Nambiar & Lucas, 2014;
Okamura *et al*., 2009;
Pat Ray *et al*., 2003). A change from baseline of 5 points or higher on most of the King’s Health Questionnaire domains represents a clinically meaningful improvement in health-related quality of life after treatment (
Kelleher *et al*., 2004).

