### Specific objectives

The overreaching aim of this study is to assess whether transcutaneous tibial nerve stimulation (TTNS) is feasible as a treatment for bladder storage symptoms in people with MS. In particular, the study will explore the feasibility and acceptability of TTNS application in people with MS by addressing the following specific objectives:

*The primary objectives are* to a) assess the recruitment and retention rates, b) investigate the completion rate and appropriateness of outcome measures by participants; c) assess safety by reporting the number of participants with adverse events; d) determine participants’ adherence to the treatment protocol, and e) assess participant’s satisfaction with TTNS application.

*The secondary objectives are to* a) evaluate the preliminary effectiveness of TTNS in managing bladder storage symptoms in MS; and to b) determine the effect of TTNS on quality of life in people with MS.

Addressing these objectives will establish a foundation for future definitive randomised trial to explore the efficacy of TTNS on bladder storage symptoms in MS.

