### Participant identification and consent

The recruitment plan is twofold: 1) Open recruitment for people with MS through MS Irelands communication channels for two months duration. This will employ the same procedures as that of our published protocol for a previous qualitative study (
[name] *et al*., 2019). A co-investigator (HD) will send recruitment letters (Appendix A, extended data (
[name], 2020)), study information sheets, and screening forms (Appendix B, extended data (
[name], 2020)) to a gatekeeper at MS Ireland who will send the emails to all people with MS and who will place the study notifications on their social medial channels. 2) In addition, our recruitment strategy will include a convenience sample of people with MS from an existing cohort of people with MS who have already participated in a qualitative telephone interview study of urinary problems. The protocol for that study, including recruitment strategies, are described in detail elsewhere (
[name] *et al*., 2019).

Interested and eligible participants will be invited to contact a member of the research team including the principal investigator (KR) or co-investigators (SC) or (HD) using the contact methods provided in the email. Once a participant contacts any member in the research team, a call will be arranged via MS Ireland’s Zoom for Healthcare account with (HD) to review eligibility and provide details of the full procedure of the study including the protocol of the nerve stimulation intervention and the outcome measures and give prospective participants the opportunity to ask questions. Participants will be made aware that they have the full right to withdraw at any stage without any explanation. Those who elect to participate will be provided with the link via email to a survey hosted on
Qualtrics Survey Software to read and sign the informed consent form, complete demographic data (Appendix C, extended data (
[name], 2020)) including the Patient Determined Disease Steps (PDDS) (
Learmonth *et al*., 2013), the International Consultation of Incontinence Questionnaire-Overactive bladder (ICIQ-OAB), King’s Health Questionnaire, the 3- day bladder diary (Appendix D, extended data (
[name], 2020)) , adverse events report diary (Appendix E, extended data (
[name], 2020)), and adherence to treatment protocol (Appendix F, extended data (

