[name], 2020)). The 3-day bladder diary, ICIQ-OAB, and King’s Health Questionnaire are to be filled twice during the study; at base line before commencing the intervention (week 0) and post commencing the intervention at the end of (week 6). Diaries including adverse events report diary and adherence to treatment protocol diary are to be filled throughout the study from (week 0) till the end of (week 6) to document any observation related to the application of the intervention. The Questionnaire for Acceptability (Appendix G, extended data (
[name], 2020)) is to be filled at the end of the intervention at the end of (week 6) to allow the researcher to determine the participant’s satisfaction level with application of TTNS.

Once participants provide the signed consent form and complete the required outcome measures, a call will be arranged using MS Ireland Zoom Healthcare account to provide details in how to apply the nerve stimulation and allow an opportunity to ask questions. After the call, all participants will be emailed a short video showing the nerve stimulation application as a reminder in how to apply the TENS unit.

The nerve stimulation unit will be posted to them by an MS Ireland’s staff member. In this package, a stamped addressed envelope will also be provided to facilitate return of the nerve stimulation unit.

During the Zoom video call participants will be given an option for paper copy of diaries instead of downloadable documents via Qualtrics Survey Software. In this scenario, HD will inform the interested participants that the hard copies of the diaries will be posted with the TENS unit.

Participants will be called by HD on a weekly basis using MS Ireland Zoom Healthcare account to check adherence to treatment protocol, any reported adverse event, discuss any issues raised up by participants, and at the end of the study will remind them to complete the outcome measures. Responses from participants will be documented to be cross-checked against the self- reported diaries for adherence and adverse events. The study will be discontinued for individual participants if participants report an adverse reaction to the application or use of TTNS.

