### Sample size

This is a pilot study and a formal sample size is not computed. We anticipate that a total of 20 participants will be recruited to the pilot study within two months.

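### The primary recruitment proportion is circular as worded, and the plan does not report the feasibility outcomes by recruitment route, so pooled figures may overstate what open recruitment would achieve

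*Protocol article*

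**What the plan says.** Under Specific objectives, the first primary objective is to "assess the recruitment and retention rates". Completion of the outcome measures, safety, adherence and satisfaction follow, also as primary objectives. The Outcomes section turns the first of these into a measure: "Feasibility will be assessed by the proportion of participants who: are recruited to the study, complete assigned outcome measures, complete the 6-week intervention". Loss to follow-up is listed under the same stem.

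Participant identification and consent describes two routes. In the first, a gatekeeper at the patient organisation is the person "who will send the emails to all people with MS and who will place the study notifications on their social medial channels". The second is a convenience sample from "an existing cohort of people with MS who have already participated in a qualitative telephone interview study of urinary problems". Anyone interested contacts the team and has a call at which eligibility is reviewed. Consent and the baseline questionnaires are then completed through an online survey. Training follows: "Once participants provide the signed consent form and complete the required outcome measures, a call will be arranged".

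Under TTNS Intervention, the six-week duration is supported by a published study in a neurogenic population and also as "preferable among participants who has been interviewed during phase II study".

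The Sample size section says "This is a pilot study and a formal sample size is not computed" and "We anticipate that a total of 20 participants will be recruited to the pilot study within two months". Statistical methods plans descriptive statistics with 95% confidence intervals for the primary outcomes and does not mention recruitment route. Specific objectives and the Conclusion both say that the results will feed into a definitive randomised trial.

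**The concern.** Recruitment is a primary outcome, and its size is what someone planning the definitive trial will look for. A proportion whose numerator and denominator are the same people carries no information, and a 95% confidence interval around it would give a false impression of precision.

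The mix of routes is a separate issue. People who have already given a research interview about their urinary problems may be readier to enrol, stay and report satisfaction than people answering an open call. If they form a sizeable part of about 20 participants, a single pooled figure for recruitment, retention or satisfaction may look better than an openly recruiting trial would find. Without the route recorded and shown, a reader cannot tell whether this happened.

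**Working it through.** **Inputs from the documents.** Anticipated recruits: 20 in two months (Sample size), that is 20 / 2 = 10 per month over both routes together. No calculation lies behind the 20, so there is no figure to reproduce. The documents give no number approached, number screened, size of the interview cohort or planned share of the 20 from each route.

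**Step 1: the recruitment proportion under different bases.** Recruitment proportion = 20 / D, with exact (Clopper-Pearson) 95% intervals. Every D other than 20 is an assumption, used only to show the range.

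| Base | D | Proportion | 95% CI |
|---|---|---|---|
| Participants, as literally worded | 20 | 100% | 83.2 to 100% |
| Assumed smaller pool, e.g. eligible people | 25 | 80% | 59.3 to 93.2% |
| Assumed larger pool, e.g. people who made contact | 40 | 50% | 33.8 to 66.2% |
| Assumed number approached | 1,000 | 2% | 1.2 to 3.1% |

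The same 20 recruits therefore give anything from 100% to 2%. The last type of base cannot be established, because the reach of social media posts is not countable. The two middle types can be: each person who contacts the team has an eligibility call, and there is a screening form. The plan does not name either as the base.

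**Step 2: completion and loss to follow-up.** Enrolled participants are the evident base here, and the proportions can be calculated: 16/20 = 80% (56.3 to 94.3%) and 18/20 = 90% (68.3 to 98.8%). One choice still matters. Training is arranged after consent and the required measures are in place. Someone who consents but abandons the baseline questionnaires therefore counts as a completion failure if the base is everyone who consented, and drops out of sight if the base is everyone treated. The condition is not absolute, since paper diaries can be posted with the device, which is a further reason to name the base at each time point.

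**Step 3: effect of mixing the routes.** Let w be the interview cohort's share of the relevant denominator. Then

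pooled rate = (1 - w) x open rate + w x cohort rate,

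so pooled rate - open rate = w x (cohort rate - open rate).

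With assumed rates of 70% (open) and 90% (cohort):

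- w = 25%: 0.75 x 70 + 0.25 x 90 = 75%, a shift of +5 points
- w = 50%: 0.50 x 70 + 0.50 x 90 = 80%, a shift of +10 points
- w = 75%: 0.25 x 70 + 0.75 x 90 = 85%, a shift of +15 points

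If the two rates are equal, the shift is zero for every w. If the cohort does worse, it is negative.

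**Step 4: what reporting by route can deliver.** With an assumed 10 participants per route, 8/10 = 80% has an exact 95% interval of 44.4 to 97.5%. Figures by route can describe but cannot support a formal comparison.

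**The case against.** The strongest reply is that most of this can be worked out from what the team will hold anyway. Contacts, eligibility calls and consents are all countable, a rate per month follows from 20 in two months, and enrolled participants are the natural base for completion and loss to follow-up. This stands. A reader might infer that none of these proportions can be calculated, and the documents do not support that. The fault lies in the wording of the recruitment measure.

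Secondly, the article condenses a fuller protocol with appendices and commits to the CONSORT extension for pilot and feasibility studies, so finer flow definitions may exist there. That is fair for the detail of the denominators. It does not repair a primary outcome that is circular in the text as published.

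Thirdly, the routes may differ less than they seem. The article says that open recruitment will reuse the procedures of the earlier qualitative study, and the open emails could reach former interviewees. The interviewees' preference is cited for one design feature only, the duration, and alongside a published study. That these interviewees are the same people as the second route is likely but not stated outright. All of this weakens any firm claim about bias, though not the case for recording the route.

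Finally, silence about route is not a rule to pool. True, but one overall descriptive summary is all that the article sets out.

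**Conclusion.** The point holds in a limited form. The recruitment measure needs rewording, because as written it is 100% by definition and the number approached is not available to replace it. The mix of routes means that the pooled recruitment, retention and satisfaction figures may overstate what an openly recruiting definitive trial would see. The size and sign of any shift are w x (cohort rate - open rate), and none of the three inputs is in the documents. The +5 to +15 points above rest wholly on assumed rates of 70% and 90% and assumed shares of 25% to 75%.

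A reader might go further and conclude that feasibility will be overstated, that the interview cohort is small and already exhausted, or that the definitive trial's recruitment would run over by a calculable number of months. The documents support none of these. They do not report how interviewees behave compared with open recruits, how large the cohort is, or how the definitive trial will recruit. Nor does it follow that the later trial should be planned from open recruits alone: the open group within about 20 participants would be small, and the trade-off is debatable. This is an inexpensive improvement to what the study can conclude and does not invalidate the design.

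**What to change.** 1. **Recruitment.** Replace the circular proportion with participants consented per month, consented/eligible, and eligible/screened, the last two among people who contact the team.
2. **Other bases.** Use everyone who consented for baseline completion, and everyone sent a device for week-6 completion, retention and adherence.
3. **Route.** Record the recruitment route at screening. Because the open emails may reach former interviewees, classify by whether the person took part in the interview study as well as by how they heard of this one.
4. **Reporting.** Give the primary outcomes by route, descriptively, as counts with exact 95% intervals where they are proportions, beside the pooled figure, so that the definitive trial can be planned with both in view.

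The cost is one added variable and a few sentences on the outcome definitions. Treatment and sample size do not change. The drawbacks are that the per-route figures will be imprecise, as Step 4 shows, and that the headline rates may look less favourable.

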### Study design

A single-arm experimental study to assess the feasibility of TTNS in MS bladder storage symptoms.

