### Statistical methods

SPSS software (Version 26.0. Armonk, NY: IBM Corp) will be used for statistical analysis:

•
*The primary outcomes* will be analysed using descriptive statistics (numbers, means, and percentage) with 95% confidence interval (CI). Medians and interquartile ranges will be reported where data are not normally distributed.

•
*The secondary outcomes* for the scores of ICIQ-OAB and King’s Health questionnaire at the baseline, and at the end of week 6 will be reported as mean scores with SD and changes in scores between baseline, and week 6 will be examined using T-tests to provide a quantitative indicator of the significance of the changes in the assessment measures following stimulation sessions. The non-parametric equivalent tests will be employed where data are non-parametric.

The incidence of nocturia, incontinence and urinary frequency and urgency will be reported across the two groups and differences will be quantified using a Chi-squared test.

The scale of Patient Perception of Intensity of Urgency Scale (PPIUS) will be assessed using descriptive statistics means and standard deviation (SD).

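### Both urgency measures are to be compared with baseline, but the analysis section gives neither a suitable within-person comparison and the 72-hour severity summary is not defined

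*Protocol article*

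**What the plan says.** The Protocol article describes its design as: "A single-arm experimental study to assess the feasibility of TTNS in MS bladder storage symptoms". Under Participant identification and consent, the bladder diary and questionnaires are completed at baseline and at the end of week 6.

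Under Outcomes, among the secondary measures: "Severity and intensity of urgency will be assessed using Patient Perception of Intensity of Urgency Scale (PPIUS"). The text continues: "Number of urgency episodes and severity of urgency/72 hours will be calculated and compared from baseline. The total score ranges from 0 to 4". A larger score means worse symptoms. Two quantities are therefore named, a number of episodes and a severity, both over 72 hours and both to be set against baseline.

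Under Statistical methods, three sentences matter:

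- For ICIQ-OAB and King's Health Questionnaire: "changes in scores between baseline, and week 6 will be examined using T-tests", with non-parametric equivalents where needed.
- For diary symptoms, urgency included, a chi-squared test is named: "The incidence of nocturia, incontinence and urinary frequency and urgency will be reported across the two groups and differences will be quantified using a Chi-squared".
- For the urgency scale: "The scale of Patient Perception of Intensity of Urgency Scale (PPIUS) will be assessed using descriptive statistics means and standard deviation (SD").

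**The concern.** Outcomes commits the trial to a baseline comparison of two urgency quantities, and the analysis section does not provide a matching analysis for either. Severity gets a mean and an SD, with no change, interval or time points named. The episode count becomes an incidence, tested by a method meant for independent groups.

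Urgency is one of the storage symptoms named in the inclusion criteria. Preliminary effectiveness on storage symptoms is a secondary objective, intended to inform a definitive randomised trial. What such a trial would use from this study is the mean within-person change and its SD. The stated analyses need not report either for urgency.

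The wording about a total score from 0 to 4 adds a second problem. It does not say how several ratings over three days become one number per person. Different summaries can give different answers from the same diary, and the choice is left open until the data are in.

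**Working it through.** **Step 1: set promise against analysis.**

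| Quantity in Outcomes | Promised | Statistical methods |
|---|---|---|
| Number of urgency episodes per 72 h | Comparison with baseline | Not analysed as a count; urgency incidence by chi-squared across two groups |
| Severity of urgency per 72 h (PPIUS) | Comparison with baseline | Mean and SD only |
| ICIQ-OAB and King's Health Questionnaire scores | Symptom and quality-of-life scores | Mean and SD, plus a test of change from baseline to week 6 |

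**Step 2: the chi-squared sentence.** There is one arm, so the two groups can only be the two visits. With the anticipated 20 participants, a visit-by-symptom table holds 2 × 20 = 40 records from 20 people. A standard chi-squared test treats the 40 as independent and ignores the pairing. Incidence, read as present or absent, also loses the count: a person who goes from 12 episodes to 2 in 72 hours has urgency at both visits and shows no change.

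**Step 3: what two means and SDs leave out.** The difference between the visit means estimates the mean change if the same people are in both. Its precision also needs the within-person correlation r:

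SD of change = √(s₀² + s₆² − 2·r·s₀·s₆), which is s·√(2(1 − r)) when both SDs equal s.

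The protocol gives no r. For n = 20 complete pairs, the 95% CI half-width is t × SD of change / √n, with t = 2.093 on 19 degrees of freedom and √20 = 4.472. The values of r below are assumptions, chosen to show the range.

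| r (assumed) | SD of change | 95% CI half-width |
|---|---|---|
| 0 | 1.414 s | 2.093 × 1.414 s / 4.472 = 0.66 s |
| 0.5 | 1.000 s | 2.093 × 1.000 s / 4.472 = 0.47 s |
| 0.8 | 0.632 s | 2.093 × 0.632 s / 4.472 = 0.30 s |

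The same two published SDs are compatible with intervals that differ in width by a factor of about 0.66 / 0.30 = 2.2.

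**Step 4: the 0 to 4 range.** With k ratings of 0 to 4 each, a sum runs from 0 to 4k, while a mean or a maximum runs from 0 to 4. The protocol does not give k. At k = 1 all of these agree. At k = 2 a sum already runs to 8, and at k = 6 to 24. The stated range therefore fits a single rating, a mean or a worst rating, and excludes a sum of two or more.

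The choice matters. Suppose a person has 12 episodes at week 0 and 6 at week 6, all of grade 2. The sum falls from 24 to 12, while the mean and the worst rating stay at 2.

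**The case against.** The strongest reply is that this is a secondary, preliminary outcome in a feasibility study of about 20 people with no formal sample size. Saying that a measure will be compared with baseline does not promise a hypothesis test, and means and SDs at weeks 0 and 6 do allow a descriptive comparison. This stands as far as it goes: a missing p-value is not the complaint. It does not answer Step 3, because even a descriptive comparison of paired data needs the change and its SD or interval.

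Three stronger readings are tempting, and the documents do not support them.

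- A reader might infer that the 0 to 4 score is an impossible total. The protocol never says that ratings are summed. ICIQ-OAB is described with the same total-score phrase, so the sentence may simply give the instrument's range. The defect is ambiguity.
- A reader might infer that the urgency comparison was dropped altogether. It was not, since urgency is in the chi-squared sentence. What fails is the match: incidence in place of the count, nothing on severity, and a test for independent groups.
- A reader might infer that a blank diary day will pass for improvement. The protocol does not say that an incomplete diary is counted as a full 72 hours. Handling of partial diaries, a minimum number of completed days, and the grade that counts as an urgency episode are details an article may leave to the full protocol or analysis plan.

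**Conclusion.** The point holds as a mismatch between Outcomes and Statistical methods, together with an undefined severity summary. Neither urgency quantity has a stated analysis that gives the within-person change with its precision, and the one stated urgency test does not fit one arm measured twice.

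The consequence is moderate. It affects a secondary outcome and leaves the feasibility and acceptability objectives untouched. It does limit what a later trial can take from the urgency data: on the assumptions in Step 3 (20 complete pairs, equal visit SDs, correlation between 0 and 0.8), the half-width of the interval for change could lie anywhere from 0.30 to 0.66 of a visit SD, and the reported figures would not show where. The conclusion that the analyses do not match rests on the text alone and needs none of those assumptions.

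**What to change.** In Outcomes, state that urgency severity is the mean PPIUS grade per rated void (0 to 4) for each participant at each visit. State that the number of urgency episodes is a separate variable, expressed per completed diary day. Replace the total-score wording for this scale accordingly.

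In Statistical methods, analyse both variables as the paired change from week 0 to week 6 with a 95% CI, using a paired t-test or its non-parametric equivalent, in line with the plan for ICIQ-OAB and King's Health Questionnaire. This replaces PPIUS means and SDs alone and takes urgency out of the chi-squared sentence. Visit means and SDs can still be reported alongside.

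The cost is a few sentences. The diary and scale are already collected at both visits, so no new data, visits or participants are needed.

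### The 5-point meaningful change on the King's Health Questionnaire has no stated direction and is not used in the analysis, which reads the change by t-test significance without a confidence interval

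*Protocol article*

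**What the plan says.** Under Outcomes, the protocol article sets its threshold for a meaningful gain in quality of life with the words "A change from baseline of 5 points or higher on most of the", referring to the domains of the King's Health Questionnaire. It gives neither a score range nor a direction for this questionnaire. The same section does give a direction for its other secondary measures. For the ICIQ-OAB, "The total score ranges from 0 to 16 with higher values indicating increased symptom severity". For the urgency scale (PPIUS), "The total score ranges from 0 to 4 with higher values indicating increased symptom severity". The bladder diary counts are likewise described as worse when higher.

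Under Statistical methods, the ICIQ-OAB and the King's Health Questionnaire are reported as mean scores with SD at baseline and week 6. Then "changes in scores between baseline, and week 6 will be examined using T-tests", with the stated purpose of indicating the significance of the changes, and with a non-parametric alternative. A 95% confidence interval is stated for the primary outcomes and not for these scores. The 5-point value does not appear in that section or elsewhere in the article.

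Under Sample size: "This is a pilot study and a formal sample size is not computed", and "We anticipate that a total of 20 participants will be recruited to the pilot study within two months". Quality of life is secondary objective (b) under Specific objectives.

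**The concern.** The plan names a yardstick for quality of life and then reads the result with a different one. The two answer different questions. The threshold asks whether the change is large enough to matter; the test asks whether zero change can be excluded. With about 20 people, a mean change as large as the plan calls meaningful may or may not be significant, depending on how variable the change is. If significance is the reading, a result compatible with meaningful benefit could be reported as no effect on secondary objective (b). The study is meant to prepare a definitive trial, which needs a signed estimate with its precision.

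The missing direction is a smaller matter. A threshold that is to be applied needs a sign, and the article does not supply one.

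**Working it through.** The plan has no power or sample size figure to reproduce, because it computes none.

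**Inputs**
- From the article: n = 20 anticipated; threshold 5 points; a single arm, so the change is within-person and the t-test is taken as paired.
- Assumed: two-sided 5% level (none is stated), all 20 providing both assessments, and an SD of change of 10 to 25 points for the table, because the article gives no SD.

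**Smallest observed mean change that is significant**

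This equals the half-width of the 95% confidence interval for the mean change: t(0.975, 19) × SD / √20 = 2.093 × SD / 4.472 = 0.468 × SD.

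| Assumed SD of change | Smallest significant mean change | 95% CI around an observed mean change of 5 |
|---|---|---|
| 10 | 4.7 | 0.3 to 9.7 |
| 15 | 7.0 | −2.0 to 12.0 |
| 20 | 9.4 | −4.4 to 14.4 |
| 25 | 11.7 | −6.7 to 16.7 |

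(Change is counted as positive in the improving direction.)

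**Break-even SD**

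Set 0.468 × SD = 5, which gives SD = 5 / 0.468 ≈ 10.7. Above this, an observed mean change of exactly 5 points is non-significant; below it, it is significant.

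**Power for a true mean change of 5 points**

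From the non-central t with 19 degrees of freedom and non-centrality 5 / (SD / √20):

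| SD of change | 5 | 7.5 | 10 | 15 | 20 | 25 |
|---|---|---|---|---|---|---|
| Power | 99% | 81% | 57% | 29% | 19% | 14% |

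Power falls below 80% once the SD exceeds about 7.6, and below 50% once it exceeds about 10.8. Whether the test is sensitive to 5 points thus depends on a quantity that the article does not give.

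**Can the reader recover the interval from what is reported?**

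The two means give the mean change if the same people contribute to both. The two SDs alone do not give its precision. The variance of the change is SD₀² + SD₆² − 2r·SD₀·SD₆, and the correlation r between baseline and week 6 is not among the planned summaries.

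**The case against.** Most of the case against a stronger criticism stands.

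- **Low power.** This is a feasibility study, quality of life is secondary, and the article says that no formal sample size was computed. Low power for such an outcome is not an error. A reader might infer that 20 people make the test insensitive to 5 points. The article does not support that as a flat statement: it gives no SD of change, and at an SD of 7.5 the power is 81%.
- **Direction.** The word improvement fixes the clinical sense, and the orientation of the scale is a property of a published questionnaire. A reader might infer that a 5-point rise and a 5-point fall would both count as improvement, so that a responder count would include people who got worse. That is strained, and no responder count is planned in the article. What remains is a wording gap.
- **Reliance on the test.** Means and SDs are reported as well, and there is no success rule. That is so, but the only inferential reading stated for the change is its significance.
- **Scores and domains.** The plural scores in the methods section is compatible with domain scores, so there is no contradiction.
- **Unseen documents.** A fuller protocol or an analysis plan may use the threshold. The point is therefore confined to the reading that this article itself fixes.
- **The fix is no more conclusive.** At SDs of 15 to 25, an interval around a mean of 5 still includes both zero and values above 10. This is true. But the interval shows that uncertainty, which a non-significant result on its own can hide.

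**Conclusion.** The point holds as a minor improvement to a secondary outcome. Two facts do not depend on any assumption: the 5-point threshold is stated without a direction, and the article's methods do not use it, relying on t-test significance with no confidence interval stated for the change.

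The possible disagreement between the two yardsticks is conditional. With 20 pairs and a two-sided 5% level, it arises for an observed mean change of 5 points if the SD of change is above about 10.7 points, and not below that. No primary feasibility objective is affected.

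**What to change.** 1. **Outcomes:** state the scoring direction of the King's Health Questionnaire and write the threshold as a change of at least 5 points in the improving direction. The present sentence refers to most domains, so name those to which the threshold applies.
2. **Statistical methods:** for each domain, report the mean within-person change from baseline to week 6 with its 95% confidence interval, interpreted against 5 points where the threshold applies. Present any p-value as descriptive only.
3. **Optional:** add the number of participants who improved by at least 5 points, stayed within 5 points, or worsened by at least 5 points.

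The cost is about two sentences and a small table from data already being collected. The downside is a less decisive headline than a p-value.
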